## Abstract

**Background:**

Speech impairment is a common symptom of Parkinson’s disease (PD) that worsens with disease progression and affects communication and quality of life. Current pharmacological and surgical treatments for PD have inconsistent effects on speech impairment. The cerebellum is an essential part of sensorimotor network that regulates speech production and becomes dysfunctional in PD. Continuous theta-burst stimulation (cTBS) is a non-invasive brain stimulation technique that can modulate the cerebellum and its connections with other brain regions.

**Objective:**

To investigate whether cTBS over the right cerebellum coupled with speech-language therapy (SLT) can improve speech impairment in PD.

**Methods:**

In this randomized controlled trial (RCT), 40 patients with PD will be recruited and assigned to either an experimental group (EG) or a control group (CG). Both groups will receive 10 sessions of standard SLT. The EG will receive real cTBS over the right cerebellum, while the CG will receive sham stimulation. Blinded assessors will evaluate the treatment outcome at three time points: pre-intervention, post-intervention, and at a 12-week follow-up. The primary outcome measures are voice/speech quality and neurobehavioral parameters of auditory-vocal integration. The secondary outcome measures are cognitive function, quality of life, and functional connectivity determined by resting-state functional magnetic resonance imaging (fMRI).

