### Primary outcomes

#### Voice quality

Participants will perform an array of speech tasks designed to assess various aspects of their speech functions. These tasks consist of sustained vowel phonation, reading a specified passage (Chinese version of “The North Wind and the Sun” that was developed by the International Phonetic Association), spontaneous speech production, a pitch range task that involves gliding the voice from the lowest to the highest pitch and vice versa, as well as a diadochokinetic task that requires rapid and alternative articulatory movements (“pa-tak-ka”). Vocal sound pressure level (SPL), voice *f*_o_, maximum phonation time (MPT), and formant frequencies will be analyzed for sustained vowel phonation. Vocal SPL, speech rate, and syllable repetition rate will be analyzed for speech tasks.

In addition, perceptual voice quality will be assessed using the Japanese GRBAS scale that consists of 5 items: grade, rough, breathiness, asthenia and strain (Moro-Velazquez et al., 2021). To minimize inter-rater variability and enhance reliability of this perceptual evaluation, we will involve three experienced raters, each skilled in evaluating speech disorders associated with PD, to independently assess the speech samples using the GRBAS scale. These raters independently evaluate all speech samples, and their scores are averaged to obtain the final GRBAS ratings. All raters will undergo an alignment process to standardize scoring methods and criteria prior to the start of the study. Furthermore, intra-class correlation coefficients (ICCs) will be calculated to quantitatively measure inter-rater reliability and control for any potential variability.

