#### Neurobehavioral changes of vocal motor control

The FAF paradigm will be used to measure neurobehavioral changes in auditory-vocal integration in patients with PD before and after TMS intervention, which will reflect their ability to integrate auditory feedback and motor control for speech processing. They will be instructed to produce sustained phonations while exposed to unexpected pitch perturbations in auditory feedback, with vocal and electroencephalographic (EEG) signals recorded simultaneously (see details below). The magnitude and latency of vocal responses will be measured as behavioral responses, while the P1, N1, and P2 components of the event-related potentials (ERPs) will be measured as neurophysiological responses.

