#### EEG data

EEG data will be recorded using a 64-electrode Geodesic Sensor Net (Electrical Geodesics Inc., Eugene, OR, USA) connected to a high input-impedance Net Amps 400 amplifier (Electrical Geodesics Inc., Eugene, OR, USA). The EEG signals will be referenced to the vertex (Cz) and digitally sampled at 1 kHz using NetStation software (v.5.4, Electrical Geodesics Inc., Eugene, OR, USA). TTL pulses will be sent to the EEG recording system via an experimental synch Deutsches Institut für Normung (DIN) for synchronization of voice and EEG signals. The impedance levels of individual sensors will be kept below 50 kΩ throughout the recording, as this amplifier accepts scalp-electrode impedances up to 60 kΩ (Ferree et al., 2001).

The EEG signals will be analyzed offline using NetStation software. They will be band-pass filtered with cut-off frequencies of 1–20 Hz and segmented into epochs ranging from 200 ms before to 500 ms after perturbation onset. An artifact detection procedure will be applied to identify bad trials, during which trials whose voltage values exceed ± 55 μv of the moving average over an 80-ms window will be rejected from further analysis. After re-referencing to the average of the electrodes on each mastoid, artifact-free trials will be averaged and baseline-corrected (−200 ms to 0) to generate an overall ERP response for each condition. A total of 24 electrodes in three regions of interest (ROIs) will be selected for statistical analysis (Dai et al., 2022; Lin et al., 2022): frontal area, including AF3, AFz, AF4, F5, F3, F1, Fz, F2, F4, and F6; fronto-central area, including FC5, FC3, FC1, FCz, FC2, FC4, and FC6; and central area, including C5, C3, C1, Cz, C2, C4, and C6. The amplitudes and latencies of the P1, N1 and P2 components will be extracted from the averaged ERPs for each ROI.

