### Statistical analysis

Statistical analyses of clinical and behavioral parameters will be performed using SPSS software (v. 20.0). All patients with PD who have at least one post-intervention assessment will be included in the analysis. Gender differences between groups will be assessed using a chi-square test. Baseline measures will be compared between groups using two-sample *t*-tests. A 2 × 3 two-way repeated-measures analysis of variance (RM-ANOVA) with factors of group (real cTBS, sham cTBS) and time (pre-intervention, post-intervention, 12-week follow-up) will be used to investigate the effects of cerebellar cTBS on speech functions, neurobehavioral changes of vocal motor control, and quality of life. *Post hoc* pairwise correction will be performed using Bonferroni comparison adjustment. Pearson analysis will be used to examine correlations between neurophysiological and behavioral measures. A *p*-value < 0.05 in a two-tailed test will be considered statistically significant.

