## Conclusion

This protocol will provide novel insights into the role of the cerebellum in the treatment of speech impairment in PD and its potential therapeutic benefits. If our hypothesis is confirmed, this protocol will support the notion that cerebellar c-TBS can be a safe, effective, and non-invasive intervention for addressing speech impairment in PD, which can complement or enhance existing behavioral SLT approaches. This protocol will also contribute to advancing our understanding of the neural mechanisms underlying the improvement of speech impairment in PD through the modulation of the cerebello-thalamo-cortical networks using non-invasive brain stimulation techniques. The findings of this study may have important implications for the development of new therapeutic strategies and the improvement of clinical outcomes for patients with PD who suffer from speech impairments.

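### Two whole domains are primary (about 32 variables read literally, 16 read leniently), each judged at 0.05, with no error control across them

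*Protocol article*

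**What the plan says.** The Abstract sets the primary outcomes as two domains: "The primary outcome measures are voice/speech quality and neurobehavioral parameters of auditory-vocal integration". Table 1 lists voice quality, vocal response and ERP under primary outcomes.

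The detail follows in the body of the article:

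- Voice quality, vowel task: SPL and voice fundamental frequency, and then "maximum phonation time (MPT), and formant frequencies will be analyzed for sustained vowel phonation".
- Voice quality, speech tasks: "Vocal SPL, speech rate, and syllable repetition rate will be analyzed for speech tasks".
- Voice quality, perceptual: the "GRBAS scale that consists of 5 items: grade, rough, breathiness, asthenia and strain", with three raters' scores averaged.
- Neurobehavioral changes of vocal motor control: "The magnitude and latency of vocal responses will be measured as behavioral responses", with P1, N1 and P2 as the neurophysiological responses.
- EEG data: three scalp regions of interest are defined, and "The amplitudes and latencies of the P1, N1 and P2 components will be extracted from the averaged ERPs for each ROI".

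Statistical analysis applies a 2 × 3 repeated-measures ANOVA (group, time) to speech functions, vocal motor control and quality of life, with two-tailed p below 0.05 as the criterion. On multiplicity it says that post hoc "pairwise correction will be performed using Bonferroni comparison adjustment". The only other correction is FDR, in the MRI data section, for connectivity, which is a secondary outcome.

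The Conclusion then reads: "If our hypothesis is confirmed, this protocol will support the notion that cerebellar c-TBS can be a safe, effective, and non-invasive intervention".

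**The concern.** A confirmatory trial needs to say which result decides it. Here the primary label covers every acoustic, perceptual, vocal-response and ERP variable listed, and each is judged at the full 0.05. A Bonferroni step inside one ANOVA protects the comparisons among its time points or groups. It does nothing about the number of ANOVAs.

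Two things are at stake. First, the probability of a nominally significant primary result under an inactive treatment is well above 5%. Second, the trial's objective is speech impairment, but the primary set mixes speech measures with laboratory measures of the response to pitch perturbation. The plan does not say which of these must succeed before cTBS is called effective for speech.

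**Working it through.** **The plan's own error calculation.** The Sample size section uses partial η² = 0.559, alpha 0.05, power 0.95 and two groups, and reports N = 16.

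- f = √(0.559 / 0.441) = 1.126.
- With the SPSS-type effect size, λ = f² (N − k)(m − 1). For k = 2 groups, m = 2 measurements and N = 16, λ = 1.268 × 14 × 1 = 17.7.
- The power is 0.974, and 16 is the smallest equal-group N that reaches 0.95. So the stated 16 reproduces. (It needs two measurements, while the planned ANOVA has three time points; that is a separate matter.)

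The relevant feature is that the calculation allows for one test at 0.05.

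**Counting the primary variables.**

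| Group | Literal | Lenient |
|---|---|---|
| Vowel: SPL, fundamental frequency, MPT, formants (counted once) | 4 | 4 |
| Speech tasks: SPL (counted once), speech rate, syllable repetition rate | 3 | 3 |
| GRBAS | 5 items | 1 score |
| Vocal response: magnitude, latency | 2 | 2 |
| ERP: 3 components × amplitude and latency × regions | 3 × 2 × 3 = 18 | 3 × 2 = 6 |
| Total | 32 | 16 |

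Per-region testing is the more literal reading, because values are extracted for each region and the ANOVA has no region factor. Neither count splits the +200 and −200 cent shifts.

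**Chance of at least one significant primary result when cTBS does nothing.** One group by time test per variable, each at 0.05.

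- Independent tests: 1 − 0.95^n. For n = 32 this is 1 − 0.194 = 0.806. For n = 16 it is 1 − 0.440 = 0.560.
- Expected false positives: 32 × 0.05 = 1.6, or 16 × 0.05 = 0.8, whatever the correlation.
- Correlated tests: equicorrelated normal test statistics, two-sided cut-off 1.96. The correlations are assumptions, because the documents give none.

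| Common correlation | 32 tests | 16 tests |
|---|---|---|
| 0 | 81% | 56% |
| 0.5 | 52% | 37% |
| 0.7 | 35% | 26% |
| 0.9 | 17% | 15% |

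A block structure for the 32 tests (0.9 between regions for the same ERP measure, 0.3 elsewhere) gives 61%.

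**For scale.** Bonferroni over 32 variables would need 0.05 / 32 = 0.0016 per test. Over 16 it would need 0.05 / 16 = 0.0031.

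**The case against.** The other side has several fair points.

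*The count is a reading.* The article never gives a number of tests. It does not say that the five GRBAS items are tested separately, and the 18 ERP tests are inferred from extraction by region together with a two-factor model. This stands: 32 is not a minimum, and 16 is a possible reading.

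*Independence is implausible.* Of the 32 variables, 18 are ERP measures from the same recordings. This also stands. A reader might infer that a false primary success is more likely than not. For 32 tests that holds only up to a common correlation of about 0.5; for 16 tests it already fails at 0.5. Inflation well above 5% does hold throughout.

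*No passage says that any one result suffices.* Correct. A reader might infer that efficacy could be claimed from any single variable, such as an ERP latency. That is drawn from the absence of a success rule. The Conclusion makes its claim conditional on the hypothesis.

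*The hypothesis is about speech.* A reader of the Discussion might infer that the only hypothesis is reduced vocal adjustment to perturbed feedback, so that a laboratory effect alone would be turned into a treatment claim. The Introduction states a hypothesis about improving speech impairment, and the Objective agrees with it. The documents therefore contain both hypotheses, and the Conclusion does not say which one it means.

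*An analysis plan may add an adjustment.* It may, and the mere absence of such detail from an article would be no finding. But the choice of primary outcome belongs to the protocol. This one makes the choice explicitly in the Abstract, Table 1 and a dedicated section, and states the significance criterion and the scope of its correction.

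**Conclusion.** The point holds in this form: the protocol fixes the primary outcome as two whole domains, judges each variable at two-sided 0.05, and states no control of error across them. Under no effect, the chance of at least one significant primary result runs from about 15% (16 tests, correlation 0.9) to about 81% (32 independent tests). The lowest figure is still about three times the nominal 5%.

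The range rests on one group by time test per variable, on the two readings of the count, and on assumed common correlations. The size within that range cannot be settled from the documents. The direction can, and it is serious enough to correct before unblinding.

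**What to change.** Before unblinding, amend the protocol wording and the registry entry as follows.

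1. Name one speech variable at one time point as the primary endpoint that supports the efficacy claim, because the objective is speech impairment. Vocal SPL in passage reading at T1 is one example; the choice is the sponsor's.
2. Place vocal response magnitude where it cannot block the speech test. It can be a second primary endpoint under Holm (smaller p-value against 0.025, then the other against 0.05), or the next step after the speech endpoint in a fixed sequence at 0.05. It should not be the gatekeeper. Nor can the sample size be cited in favour of that, since the Sample size section does not say which variable gave the partial η² of 0.559.
3. Make the remaining acoustic, GRBAS and ERP variables secondary, with Holm or FDR within domain, or label them exploratory.
4. Tie the statement of effectiveness in the Conclusion to the speech endpoint.

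No new data or participants are needed. The costs are that most of the present primary outcomes become supportive, and that a split alpha loses a little power on the speech endpoint. The fixed sequence avoids that loss, but vocal response magnitude can then be formally tested only if the speech endpoint succeeds.

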**Significance:**

This trial will provide evidence for the efficacy and safety of cerebellar cTBS for the treatment of speech impairment in PD and shed light on the neural mechanism of this intervention. It will also have implications for other speech impairment attributed to cerebellar dysfunctions.

**Clinical trial registration:**

www.chictr.org.cn, identifier ChiCTR2100050543.

## Introduction

Parkinson’s disease (PD) is a neurodegenerative disease that affects motor and non-motor functions, including speech. Nearly 90% of patients with PD are affected by motor speech disorders (Logemann et al., 1978; Ho et al., 1998), characterized by hypokinetic dysarthria that involves reduced voice loudness and pitch, speech dysfluency, imprecise articulation, and monotone (Logemann et al., 1978). Motor speech disorders can occur early in the disease progression (Stewart et al., 1995) or even during the prodromal stages of PD (Postuma et al., 2012; Rusz et al., 2021), and their severity tends to decline progressively (Holmes et al., 2000; Skodda et al., 2009, 2011). These disorders lead to impaired communication function and reduced quality of life (Miller et al., 2006; Pell et al., 2006; Hall et al., 2011).

Despite the prevalence of motor speech disorders in PD, the current treatment options are limited and inconsistent. Dopaminergic medication, the main pharmacological therapy for motor symptoms in PD, has shown mixed effects on speech function, with some studies reporting slight improvement in acoustic-phonatory characteristics, respiratory parameters, and speech intelligibility (Goberman et al., 2002; De Letter et al., 2007; Ho et al., 2008; Okada et al., 2015), whereas others showing no effect or even a worsening of speech function (Plowman-Prine et al., 2009; Fabbri et al., 2017). These findings suggest that other underlying mechanisms, beyond dopaminergic deficits, may contribute to speech impairment in PD. Deep brain stimulation (DBS) of the subthalamic nucleus (STN), a surgical therapy for motor symptoms in advanced PD, has also shown variable effects on speech function, with some studies reporting improvement in oral motor and voice features (Gentil et al., 2003; Dromey et al., 2010; Sidtis and Sidtis, 2017) whereas others reporting no effect or even a deterioration of speech function (Tripoliti et al., 2011; Xu et al., 2018; Tanaka et al., 2021; Vos et al., 2021; Catalano Chiuve et al., 2022). Moreover, there is evidence that the effects of DBS on speech function may depend on the stimulation parameters or task demands (Klostermann et al., 2008; Tripoliti et al., 2008). This discrepancy in response to DBS between limb motor symptoms and speech impairment further underscores the notion that speech impairment in PD may involve mechanisms that are not strictly dopaminergic in nature. As such, it is important to consider non-pharmacological or non-invasive treatment approaches for managing speech impairment in PD.

To date, speech-language therapies (SLTs) are often recommended as a complementary intervention. One of SLTs specifically designed for hypokinetic dysarthria in PD is the Lee Silverman Voice Treatment (LSVT^®^ LOUD) (Ramig et al., 1996), which aims to enhance vocal loudness and improve speech quality. Previous studies have demonstrated immediate and long-term (12–24 months) benefits of LSVT^®^ LOUD in terms of vocal loudness, pitch variability, and speech intelligibility (Ramig et al., 2001; Sapir et al., 2007; Li et al., 2021). However, this treatment is constrained by high-effort and intensive vocal training, which can lead to a high dropout rate among patients. Therefore, there is a need to develop new alternative methods that provide more accessible and sustainable benefits for speech impairment in PD.

Repetitive transcranial magnetic stimulation (rTMS) is a non-invasive method that can modulate cortical excitability by applying magnetic pulses over the scalp. Several meta-analyses have shown a significant medium-sized effect of rTMS on alleviating PD motor symptoms (Chou et al., 2015; Chung and Mak, 2016). However, there is limited and conflicting evidence for rTMS on speech impairment in PD. Early studies focused on applying high-frequency rTMS over certain brain regions in patients with PD, such as the left primary orofacial sensorimotor (SM1), primary motor area (M1) associated with the hand or mouth, and the left dorsolateral prefrontal cortex (DLPFC), but found inconsistent effects on their voice quality and loudness (Dias et al., 2006; Hartelius et al., 2010; Eliasova et al., 2013). For example, while improved vocal pitch and loudness, tongue movement, and voice quality in patients with PD were found after high-frequency rTMS over the left SM1 or the M1-mouth area (Dias et al., 2006; Eliasova et al., 2013), no such benefits were not found when high-frequency rTMS was applied over the left DLPFC or the M1-hand area (Dias et al., 2006; Hartelius et al., 2010; Eliasova et al., 2013). Recently, low-frequency rTMS over the right superior temporal gyrus (STG) led to improved speech articulation in patients with PD, which was associated with enhanced right STG activation during sentence reading (Brabenec et al., 2019) and resting-state functional connectivity (FC) between STG and SM1 (Brabenec et al., 2021). Therefore, there is mixed evidence regarding the efficacy of TMS intervention for PD speech impairment, which may be related to variations in stimulation protocol and treatment outcomes. The choice of stimulation parameters, including modality and location, may have differential impacts on the intervention effects on speech impairment in PD. On the other hand, conventional outcome measures, such as acoustic [e.g., fundamental frequency(*f*_o_), intensity, formant frequency] and/or perceptual (e.g., phonetics score, speech intelligibility) assessments (Dias et al., 2006; Eliasova et al., 2013; Brabenec et al., 2021), may not fully capture the multifaceted aspects of speech improvement and the dynamic nature of speech communication. Therefore, future studies should carefully consider these factors when designing and evaluating rTMS interventions for speech disorders in PD.

Speech production is a complex process that requires the coordination of both cortical and subcortical regions (Hickok, 2012). Within this network, the cerebellum plays an important role in supporting various aspects of speech production, such as motor planning, timing, sequencing, coordination and error correction (Ackermann et al., 1998; Chen and Desmond, 2005; Ben-Yehudah et al., 2007; Manto et al., 2012; Marien et al., 2014). Neuroimaging studies have revealed altered cerebellar activity and abnormal functional connectivity between cerebellum and other brain regions in PD (Yu et al., 2007; New et al., 2015; Yang et al., 2016; Manes et al., 2018). On the other hand, the cerebellum has been shown to be activated during sensorimotor control of speech production, as evidenced by increased cerebellar activity in response to first formant (*F*_1_) perturbations (Tourville et al., 2008) and jaw perturbations (Golfinopoulos et al., 2011) during speech production. Clinically, patients with spinocerebellar ataxia (SCA) have shown reduced adaptive responses to speech *F*_1_ perturbations (Parrell et al., 2017) and enhanced reflexive responses to vocal pitch perturbations (Houde et al., 2019; Li et al., 2019). Similarly, impaired sensorimotor control of vocal production has been found in patients with PD, as reflected by abnormal vocal compensations for altered loudness, pitch, or formant during vocal/speech production (Liu et al., 2012; Chen et al., 2013; Huang et al., 2016; Mollaei et al., 2016). Together, these findings suggest that the cerebellum may be impaired or dysfunctional in patients with PD, which may contribute to their speech impairment.

Given the importance of the cerebellum in speech production and the evidence of cerebellar dysfunction in PD, it is reasonable to hypothesize that modulating cerebellar activity could improve speech impairment in patients with PD. To test this hypothesis, the present protocol will apply continuous theta burst stimulation (cTBS), a specific form of rTMS that induces long-lasting inhibitory effects on neuronal excitability (Huang et al., 2005), over the right cerebellum in patients with PD and evaluate their speech function before and after stimulation. The present protocol chooses the cTBS protocol based on the observation of enhanced auditory-motor integration for vocal pitch regulation in patients with SCA (Lin et al., 2022) as a consequence of inhibiting cerebellar activity. The right cerebellum is selected as the target site based on the following considerations. Activation of the right cerebellum has been observed during verbal generation tasks (Riecker et al., 2000; Stoodley, 2012), verbal working memory (Riva and Giorgi, 2000), voiced speech (Schulz et al., 2005), and compensatory adjustment of speech *F*_1_ (Tourville et al., 2008). Moreover, studies employing cTBS have reported impaired verbal working memory and reduced accuracy in lexical tasks when the right cerebellum was stimulated, a phenomenon that was not observed when cTBS was applied over the contralateral region (Argyropoulos, 2011; Tomlinson et al., 2014). Additionally, clinical evidence has shown that damage to the right cerebellum is often associated with impaired speech articulation and planning (Silveri et al., 1998; Ackermann et al., 2007). More importantly, recent tDCS and cTBS studies have established a causal relationship between the right cerebellum and speech production. For example, anodal tDCS and cTBS over the right cerebellum resulted in increased (Peng et al., 2021) and decreased (Lin et al., 2022) vocal compensations for pitch perturbations, respectively. Interestingly, this causal relationship was absent when the left cerebellum was stimulated with TBS (Liu et al., 2022). In addition, increased speech compensations for *F*_1_ perturbations were found when anodal tDCS was applied over the right cerebellum (Lametti et al., 2018).

In this protocol, patients with PD will be divided to two groups: one group will receive real cTBS over the right cerebellum, while the other group will receive sham stimulation. Before and after TMS intervention, they will perform a battery of speech tasks to assess their voice loudness and pitch, speech fluency, articulation accuracy, and prosodic variation. We will also evaluate auditory-motor control of vocal production using the frequency-altered feedback (FAF) paradigm (Burnett et al., 1998), which involves manipulating auditory feedback during vocalization and measuring compensatory changes in vocal output. Recent evidence has shown a significant correlation between reduced compensatory responses to vocal pitch errors and improved vocal intensity during passage reading in patients with PD following LSVT^®^ LOUD (Li et al., 2021). To investigate the neural mechanisms underlying the effects of cerebellar cTBS on speech impairment in PD, we will employ resting-state functional magnetic resonance imaging (rs-fMRI) to measure FC between the cerebellum and other brain regions. This protocol will provide new insights into the cerebellar contribution to PD speech disorders and potential therapeutic interventions.

